## Abstract

**Background:**

Stroke survivors often face challenges in motor learning and motivation during rehabilitation, which can impede their recovery progress. Traditional rehabilitation methods vary in effectiveness, prompting the exploration of novel approaches such as reward strategies. Previous research indicates that rewards can enhance rehabilitation motivation and facilitate motor learning. However, most reward paradigms have utilized fixed reward amounts, which also have limitations. Exploring alternative, more effective reward strategies, such as probabilistic rewards, is warranted to optimize stroke patient rehabilitation.

**Methods:**

A total of 81 stroke patients will be recruited and randomly assigned to control, fixed reward, or probabilistic reward groups at a ratio of 1:1:1 using a randomized number table method. Participants will undergo 10 days of daily hand motor function rehabilitation training, with sessions lasting 20 min each. The training will involve pegboard tests and box and block tests. Control group participants will receive standard training, while fixed reward group members will receive monetary incentives for completing tests, and probabilistic reward group members will have the chance to win monetary rewards through a lottery box. Rehabilitation motivation and motor performance and functional near-infrared spectroscopy brain imaging will be conducted at designated time points. The primary outcome measure is the stroke rehabilitation motivation scale, and the second outcome measures include motor performance, simple test for evaluating hand function, motivation and pleasure scale self-report, and Pittsburgh rehabilitation participation scale.

**Discussion:**

Reward-based training enhance rehabilitation participation and adherence, it also improve motor learning speed and memory retention of stroke patients. The fixed reward applied in the past studies could diminish the sensitivity of stroke patients to rewards, while probabilistic reward may provide unpredictable or variable incentives or reinforcements for motor rehabilitation. This study will compare the efficacy of different reward strategies in enhancing motor learning ability and rehabilitation motivation among stroke patients. By conducting a randomized controlled trial, the study seeks to provide valuable insights into optimizing stroke rehabilitation protocols and improving patient outcomes.

**Clinical Trial Registration:**https://www.chictr.org.cn/, ChiCTR2400082419.

## Introduction

Stroke is a leading cause of long-term disability worldwide, often resulting in motor impairments that significantly impact the quality of life of affected individuals (1). Successful rehabilitation following stroke relies not only on the effectiveness of interventions but also on patients’ motivation to engage in therapy and their ability to learn and retain new motor skills (2). However, stroke survivors frequently experience challenges in motor learning due to neuroplastic changes in the brain and may lack motivation to participate in rehabilitation activities (3).

Motor learning is a complex process involving the acquisition, retention, and transfer of new motor skills through practice and experience. Stroke survivors often exhibit impairments in motor learning due to disruptions in neural circuits, alterations in sensorimotor integration, and impaired motor planning. Traditional rehabilitation approaches focus on repetitive practice and task-specific training to promote motor recovery. However, variability in individual responsiveness to rehabilitation interventions highlights the need for innovative strategies to enhance motor learning outcomes in stroke patients (4).

Motivation plays a critical role in driving engagement and adherence to rehabilitation programs. Stroke survivors may face various barriers to motivation, including frustration, lack of interest, and perceived lack of progress (5, 6). Providing meaningful incentives and rewards has been shown to enhance motivation and promote active participation in rehabilitation activities. Reward-based strategies, such as positive reinforcement, goal-setting, music and feedback, can help increase patients’ motivation and adherence to therapy regimens (7, 8).

Reward strategies have been increasingly integrated into rehabilitation programs to enhance patient motivation and engagement. Positive reinforcement, in the form of praise, encouragement, or tangible rewards, can reinforce desired behaviors and increase the likelihood of their repetition (9–11). Goal-setting allows patients to establish clear objectives and track their progress, providing a sense of achievement and motivation to continue rehabilitation efforts. Feedback mechanisms, such as visual or auditory cues, provide real-time information about performance, enabling patients to adjust their efforts and improve motor learning outcomes (12). However, in the majority of previous studies, the reward approach has been predominantly fixed. Fixed reward involves providing consistent and predictable incentives or reinforcements for desired behaviors or achievements. Examples of fixed rewards in stroke rehabilitation include tokens, or tangible rewards given consistently for meeting specific therapy goals or milestones. As time progresses, the sensitivity of participants to rewards gradually diminishes, which appears to limit the effectiveness of rewards. In contrast, another reward strategy, probabilistic reward, entails providing unpredictable or variable incentives or reinforcements for desired behaviors. This might include occasional praise, surprise rewards, or lottery-based incentives for demonstrating progress in therapy. Fixed rewards provide clear expectations and reinforcement for desired behaviors, promoting motivation and adherence to therapy regimens. On the other hand, probabilistic rewards create excitement and anticipation, stimulating motivation and engagement in therapy activities (13).

Previous studies have explored the effectiveness of fixed reward-based training in stroke rehabilitation, but there remains a need for comparative research to determine which approach—fixed or probabilistic reward—is more sensitive and efficient. The optimal types and delivery methods of rewards in stroke rehabilitation remain underexplored. Addressing this gap in the literature will provide valuable insights into optimizing stroke rehabilitation protocols and ultimately improving patient outcomes. This study aims to compare the efficacy of fixed and probabilistic reward strategies in enhancing motor learning ability and rehabilitation motivation in stroke patients, and seeks to inform the development of evidence-based rehabilitation protocols and improve patient outcomes following stroke.

## Methods and analysis

### Study design

This clinical trial adopts a single-center, single-blind randomized controlled design to investigate the efficacy of different reward strategies in enhancing motor rehabilitation outcomes among stroke patients. The study aims to enroll a total of 81 participants with residual motor deficits in their right upper limbs following a stroke. Participants will be randomly assigned to control group, fixed reward group or probabilistic reward group. Allocation will be conducted using a computer-generated randomization sequence to ensure an equal distribution of participants across the groups. Throughout the intervention period, all participants will receive standard rehabilitation training along with hand motor function training (20 min per day). The hand training was conducted using the pegboard test and the Box and Block Test (BBT) combined with different reward strategies. Rehabilitation motivation, motor performance evaluations and objective assessments will be conducted at designated time points.

### Participants

This research will recruit subjects from the department of rehabilitation medicine at the Second Rehabilitation Hospital of Shanghai. Patient recruitment will commence on May 1, 2024. Recruitment methods will primarily include advertising, physician referrals, and internet recruitment. All subjects will be initially screened by the principal investigator before enrollment. Patients who meet the recruitment criteria and express interest will be individually informed of the trial details and consent requirements (Figure 1). Patients will sign a paper version of the informed consent form after fully understanding the benefits and risks of this study.

**Figure 1 fig1:**
[figure not shown]
Flowchart of study design. BBT, Box and Block Test; fNIRS, Functional Near-Infrared Spectroscopy; MAP-SR, Motivation and Pleasure Scale Self-Report; PRPS, Pittsburgh Rehabilitation Participation Scale; SRMS, Stroke Rehabilitation Motivation Scale; STEF, Simple Test for Evaluating Hand Function.

**Inclusion Criteria**: (1) Patients diagnosed with stroke based on clinical assessment and comprehensive imaging examinations. First onset of stroke; duration of illness ≥1 month. (2) The impairment of motor function in the right upper limb (including the forearm and hand). (3) Age between 18 and 80 years, irrespective of gender, and right-handed. (4) Brunnstrom stages III to V. (5) Able to tolerate assessment sessions lasting from half an hour to one hour. (6) Participants and their legally authorized guardians understand and agree to participate in this study, and jointly sign the informed consent form.

**Exclusion Criteria**: (1) Patients with severe systemic diseases such as cardiopulmonary disorders, uremia or heart failure that render them unable to tolerate rehabilitation treatment. (2) Diagnosed with psychiatric disorders, severe depression, or having a family history of psychiatric disorders (HAMD-17 scores > 24). (3) Severe joint contractures (active range of motion of the upper limb is less than half of the normal range without eliciting pain). (4) Presence of consciousness disorders due to any cause, Glasgow coma score < 15 (14). (5) Auditory or visual impairments that may affect assessment and treatment. (6) Use of medications altering cortical excitability (antiepileptic drugs, sedatives, etc.). (7) Significant pain or mental disorders (visual analog scale > 6).

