### Randomization, allocation, and blinding

The randomization procedure employed in this study adhered to rigorous standards, utilizing a randomized number table method. Subjects were allocated randomly into three groups (control group, fixed reward group and probabilistic reward group) at a precise ratio of 1:1:1, ensuring that each group consisted of 27 participants. Group allocation was meticulously executed using the sealed envelope method. Prior to participant assignment, random allocation sequences were meticulously generated and securely housed within sequentially coded, sealed, opaque envelopes. Following confirmation of subject eligibility by the researcher, envelopes were systematically unsealed, and subjects were then allocated to their respective groups.

In adherence to stringent confidentiality protocols, prior to envelope unsealing, the names and comprehensive profiles of eligible subjects were meticulously transcribed onto the exterior of each envelope. Duplicate records were also securely enclosed within, serving as a safeguard against any potential data loss or discrepancies. Furthermore, to ensure the utmost confidentiality and integrity of the allocation process, each envelope was reinforced with an additional layer of protection, such as a hardboard or tin foil insert, effectively shielding its contents from visibility under intense lighting conditions.

To uphold the scientific rigor of the study and mitigate the risk of bias, a single-blinding approach was meticulously implemented. This method ensured that assessors remained blinded to the subjects’ group allocations and the specific intervention protocols administered. Moreover, to maintain consistency and objectivity in the evaluation process, all patient training sessions and subsequent assessments were meticulously recorded. These assessments were conducted by therapists who were intentionally kept unaware of the patients’ group assignments. In case of anomalous data detected during data analysis or data verification, the designated data analyst will promptly notify both the principal investigator and the assessor. Subsequently, a comprehensive review of the recorded sessions will be conducted to verify the accuracy and reliability of the obtained results, thereby upholding the highest standards of scientific integrity and validity.

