### Outcome assessment

The components of the assessment include basic information (gender, age, duration of illness, medication history, etc.), motivation, motor performance and objective assessments. The main assessments focus on motivation and motor performance. Comprehensive video recordings of each training session will be subjected to meticulous analysis to evaluate daily motor performance. Rehabilitation motivation evaluations and functional near-infrared spectroscopy (fNIRS) measurements will be conducted at designated time points (Table 1).

**Table 1 tab1:** Recommended content for the schedule of enrolment, interventions, and assessments.

	Study period						
	Enrolment and assessment	Allocation	Training			Follow-up	
Timepoint	−D_1_	0	D_1_	D_2_–D_9_	D_10_	D_14_	D_28_
Enrolment							
Eligibility screen	X						
Informed consent	X						
Allocation		X					
Interventions							
Control group							
Fixed reward group							
Probabilistic reward group							
Assessments							
SRMS	X		X		X	X	X
MAP-SR	X		X		X	X	X
PRPS	X		X		X	X	X
Motor performance	X		X	X	X	X	X
fNIRS	X		X		X	X	X

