### Statistical analysis

Categorical variables like gender and affected side will be presented as percentages and compared using the chi-square test. Continuous variables will undergo normality assessment with the Shapiro–Wilk test and variance homogeneity examination with Levene’s test. One-Way ANOVA will compare motivation among groups before and after training, followed by Tukey’s HSD test for *post hoc* comparisons. The repeated measures ANOVA was performed to analyze changes in rehabilitation motivation scales data and average time spent in pegboard test and BBT in the three groups. Non-normal or heterogeneous data will be analyzed using the Kruskal-Wallis test, with *post hoc* tests conducted using Dunn’s test. Normal data will be presented as mean ± standard deviation, while non-normal data will be presented as median and quartiles. The significance level (P) for hypothesis testing will be set at 0.05.

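### Time since stroke has no stated upper limit and is recorded at baseline, but the motor analyses as written do not adjust for it; this costs precision and leaves chance imbalance uncorrected

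*Protocol article*

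**What the plan says.** All references are to the protocol article.

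- **Participants, inclusion criteria.** The only limit on disease stage is "First onset of stroke; duration of illness ≥1 month". The criterion "Brunnstrom stages III to V" limits motor severity, not time since stroke.
- **Participants, recruitment.** Patients come from one rehabilitation department. "Recruitment methods will primarily include advertising, physician referrals, and internet recruitment".
- **Study design; Randomization, allocation, and blinding.** The sequence is computer-generated in one section and made "utilizing a randomized number table method" in the other. Both sections name group size as the only thing balanced: "at a precise ratio of 1:1:1, ensuring that each group consisted of 27 participants".
- **Outcome assessment.** Baseline data include "basic information (gender, age, duration of illness, medication history, etc".).
- **Statistical analysis.** The stated test of change over time across the arms is this: "The repeated measures ANOVA was performed to analyze changes in rehabilitation motivation scales data and average time spent in pegboard test and BBT". Where normality or equal variance fails, the plan switches to Kruskal-Wallis with Dunn's test. No test named there carries a covariate.
- **Secondary outcomes.** Motor performance and STEF are secondary; the primary outcome is the SRMS. Table 1 follows motor performance to D28.

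**The concern.** Patients at different times after stroke may be improving at different rates whatever their arm, and all of them also receive standard rehabilitation. A repeated measures ANOVA by group and time deals with differences in starting level. It does not deal with differences in expected slope, and two patients with the same baseline score may have different expected recovery. Where slope depends on time since stroke, that variation has two effects. It sits in the error term and weakens the arm comparison, and any chance difference between arms in the mix of early and late patients shifts the estimate.

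The motor results are formally secondary, but the Introduction names motor learning as an aim and Outcome assessment says the main assessments focus on motivation and motor performance. The covariate that would address the problem is already collected.

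**Working it through.** **Inputs from the article.** 27 per arm randomised and 23 per arm evaluable. Effect size 2.34/3.47 = 0.674, which reproduces. 23/0.85 = 27.06, in line with the planned 27. Here d = 0.674 and n = 23 serve only as the plan's own yardstick, since the article gives no effect size for the motor outcomes. Whether 23 per arm delivers the stated 95% power is a separate matter.

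**Assumptions not in the article.** Share of early patients p = 0.3 to 0.5. Extra recovery in early patients 0.5 or 1.0 SD. Share of outcome variance explained by time since stroke R² = 0.10 to 0.30.

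**1. How large a chance imbalance is likely?**

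SE of the difference in early share between two arms = √(2p(1−p)/27):
- p = 0.3: √(0.42/27) = 0.125
- p = 0.5: √(0.50/27) = 0.136

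A gap of 20 points is 0.20 × 27 = 5.4 patients, so at least 6 patients. Binomial results:

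| Per arm | p | One given pair | Any pair of three |
|---|---|---|---|
| 27 | 0.3 | 10% | 23% |
| 27 | 0.5 | 13% | 29% |
| 23 | 0.3 | 15% | 31% |
| 23 | 0.5 | 18% | 38% |

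**2. What does such an imbalance do?**

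Shift = gap × recovery difference. At 20 points this is 0.20 × 0.5 = 0.10 SD, or 0.20 × 1.0 = 0.20 SD.

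Simulated one-way ANOVA on a change score with no reward effect, at 23 or 27 per arm, 100,000 trials per setting:

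| Trials considered | Unadjusted, 0.5 SD | Unadjusted, 1.0 SD | Adjusted |
|---|---|---|---|
| All | about 5% | about 5% | about 5% |
| Some pair differs by ≥20 points | 5.7–6.3% | 7.9–8.9% | about 5% |
| Some pair differs by ≥30 points | 6.6–8.7% | 10.9–15.1% | about 5% |

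**3. What does adjustment gain in precision?**

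Three-arm ANOVA, 23 per arm, one arm shifted by d. Noncentrality λ = n × d² × (2/3) / (1 − R²).
- R² = 0: λ = 23 × 0.4547 × 0.667 = 6.97, power about 63%.
- R² = 0.10: λ = 6.97/0.90 = 7.75, simulated power 67%.
- R² = 0.20: λ = 6.97/0.80 = 8.72, simulated power 73%.
- R² = 0.30: λ = 6.97/0.70 = 9.96, simulated power 79%.

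**Link between steps 2 and 3.** An early/late difference of s SD implies R² = s²p(1−p)/(1 + s²p(1−p)). This is 0.0525/1.0525 = 5% at s = 0.5, p = 0.3, and 0.25/1.25 = 20% at s = 1.0, p = 0.5. The 30% end therefore needs a stronger dependence than the early/late split of step 2. At the weak end (5%) the gain is smaller than the lowest figure above.

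**The case against.** **An omission in a condensed article.** Covariate lists and stratification details are often left to a full protocol or SAP, neither of which is shown. This stands in part. The article does not say the list is unstratified; it names no factor beyond group size, and no more should be read into that. On analysis, however, the article is not silent. It specifies particular tests, none adjusted, and one of them cannot take a covariate.

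**Type I error is inflated.** A reader might infer this, but it does not follow. Over all randomisations the unadjusted rate stays at about 5%, because the error term already reflects such variation. Only trials with a marked imbalance have a raised rate.

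**An imbalance would be reported as a reward effect.** This is also too strong. With a gap of 20 points or more, the unadjusted test rejects in roughly 6% to 9% of null trials, so usually it does not reject.

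**Patients years after stroke will be enrolled.** The eligibility and recruitment text allows it, but does not show it. The Intervention section places training in the inpatient period, which may narrow the range. The article gives no recovery rates by time since stroke, and over 10 to 28 days the difference may be modest. This objection stands, and it is why every size given here is conditional on stated assumptions.

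**Only secondary outcomes are affected.** Correct. Nothing here is argued for the SRMS.

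**Broad eligibility is a legitimate choice.** Agreed; no change to eligibility is suggested.

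**Conclusion.** The point holds as a low-cost improvement to the analysis of secondary motor outcomes, not as an error that invalidates the trial. The article sets no upper limit on time since stroke, names no balancing factor beyond group size, records duration of illness, and compares the arms without it.

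If recovery rate varies with time since stroke, two costs follow. The first is lost precision, which applies whether or not the arms are balanced. The second is a shifted estimate in the minority of trials with a marked imbalance. Both depend on the assumed early share, recovery difference and explained variance, none of which the article gives. The power figures come from a single-outcome ANOVA and indicate scale only; they do not predict the result of the repeated measures model.

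Prespecification matters because adjusting only after an imbalance has been seen would be a data-driven choice.

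**What to change.** In Statistical analysis, state that pegboard, BBT and STEF will be analysed at post-baseline visits with a repeated measures model. The model contains arm, visit, arm by visit, the baseline value of the outcome, log time since stroke, and log time since stroke by visit, with the covariates fixed before unblinding.

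For non-normal or heterogeneous motor data, replace unadjusted Kruskal-Wallis with an ANCOVA on transformed or ranked data carrying the same covariates. Without this, the adjustment would be lost whenever the fallback is used.

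The cost is a short addition to the analysis section and a few degrees of freedom. It needs no extra patients, visits or data. Stratified allocation is not proposed, because the Randomization section says the sequences were generated and sealed before assignment.

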### Sample size

The statistical software G-power (Heinrich Heine University Düsseldorf, Dusseldorf, Germany) was utilized to ascertain the sample size, with an alpha value set at 0.05, power at 0.95. By employing Cohen’s d using data extracted from a prior study by Chen et al. (15), we ascertain the mean discrepancy between groups to be 2.34 (27.54–25.2), with a pooled standard deviation approximating 3.47. Acknowledging the discrepancy in sample sizes between the two groups, the effect size is computed to be 0.674. With these parameters, the calculated sample size per group was determined to be 23 participants, summing up to 69 participants across three groups. Anticipating a dropout rate of 15%, the final sample size was adjusted, necessitating 27 participants per group, resulting in a total sample size of 81 participants.

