### Intervention

Following the completion of the informed consent process, participants will formally commence the trial protocol. Throughout the inpatient period, hand motor function rehabilitation training will be administered once daily, with each session lasting approximately 20 min. This regimen comprises three Pegboard Tests and three BBT. In the context of the pegboard test, a common assessment tool used in rehabilitation settings, motor performance is evaluated by measuring the time it takes for individuals to complete specific tasks involving moving pegs from one location to another on a pegboard. The pegboard test often varies in complexity, with tasks ranging from simple movements to more challenging ones requiring precise coordination and dexterity. The Pegboard Test will be stratified into three difficulty tiers based on training complexity: peg removal, peg insertion, and peg flipping, further classified into three levels according to peg size.

The training regimen encompasses two distinct phases. In phase one, known as the baseline assessment, the Pegboard Test evaluates the maximum difficulty level of actions that patients can successfully complete and identifies the minimum peg size. BBT training entails patients transferring blocks as swiftly as possible within a 1-min timeframe, with a 1-min inter-session rest period, during which the number of successfully transferred blocks is recorded.

Phase two entails rehabilitation training, wherein patients undergo hand motor training once daily for 10 consecutive days, employing the highest difficulty level of actions and pegs. Patients are tasked with completing all pegs expeditiously. Following each training session, there will be a 1-min rest period, after which the pegboard will be reset for three additional pegboard training sessions. Patient metrics, including maximum action difficulty, peg size, and completion time, will be meticulously documented. BBT training will adhere to the same protocol as the baseline assessment, recording the number of successfully transferred blocks within a 1-min duration, repeated thrice.

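### Brunnstrom stage is known for every patient at entry but is not in the motor analysis as described, which can cost precision (not validity) on the secondary motor outcomes

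*Protocol article*

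**What the plan says.** Inclusion criterion 4 (Participants) requires "Brunnstrom stages III to V". Stage is not mentioned again in the article.

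Allocation (Randomization, allocation, and blinding) is made "utilizing a randomized number table method". The arms are to be equal in size: "at a precise ratio of 1:1:1, ensuring that each group consisted of 27 participants". No severity factor is described there or under Study design.

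Under Intervention, each patient's peg task is set at baseline to the hardest action and smallest peg that the patient can manage, and training follows "employing the highest difficulty level of actions and pegs". Table 1 schedules motor performance on the day before allocation, on D1, D2–D9 and D10, and at D14 and D28.

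The Statistical analysis section gives the motor model as follows: "The repeated measures ANOVA was performed to analyze changes in rehabilitation motivation scales data and average time spent in pegboard test and BBT". The comparison covers all three arms, and no covariate is named. The fallback is: "Non-normal or heterogeneous data will be analyzed using the Kruskal-Wallis test", followed by Dunn's test.

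**The concern.** The trial mixes three stages of motor recovery, and improvement over four weeks may differ between them. Group-by-time is the term in the repeated measures ANOVA that tests whether the arms improve differently. The within-patient structure takes out a constant level difference between, say, a stage III and a stage V patient. It does not take out a difference in how fast they improve. That variation sits in the error term for group-by-time and widens the interval for any reward effect.

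Motor learning is one of the two stated aims, and the variable needed to recover the lost precision must already have been assessed to establish eligibility.

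**Working it through.** **Inputs from the article.** 27 patients per arm; planning effect 2.34 / 3.47 = 0.674 (Sample size), which reproduces. The outcome behind 0.674 is not named there, so it serves below only as a yardstick. The article has no figure of its own on stage and improvement.

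**Assumptions (not in the documents).** Stages III, IV and V in equal thirds. Mean improvement is 0, d/2 and d in the three stages, with d = 0, 0.5, 1.0 or 1.5, in units of the SD of change that remains within stage (residual SD = 1).

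**Step 1, variance due to stage.** The mean gain is d/2, so the variance is [(d/2)² + 0 + (d/2)²] / 3 = d²/6. The total variance of change is 1 + d²/6, and the share explained by stage is R² = (d²/6) / (1 + d²/6).

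**Step 2, precision of a two-arm contrast in change.**
- Stage removed: half-width = 1.96 × √(2/27) = 0.533.
- Stage left in: half-width = 0.533 × √(1 + d²/6).

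**Step 3, equivalent extra patients.** 1/(1 − R²) − 1 = d²/6.

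**Step 4, power** of a two-sided two-sample t-test on change at 27 per arm, for an effect of 0.674 residual SD (noncentral t).

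| d | R² | Half-width unadjusted | Half-width adjusted | Worth in extra patients | Power unadjusted | Power adjusted |
|---|---|---|---|---|---|---|
| 0 | 0 | 0.533 | 0.533 | 0% | 68% | 68% |
| 0.5 | 0.040 | 0.544 | 0.533 | 4% | 66% | 68% |
| 1.0 | 0.143 | 0.576 | 0.533 | 17% | 61% | 68% |
| 1.5 | 0.273 | 0.626 | 0.533 | 38% | 55% | 68% |

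**Step 5, check by another route.** A simulation of the three-arm test on a change score (the same as group-by-time with two time points) used 27 per arm, equally likely stages, and one arm shifted by 0.674 SD of *total* change. Power unadjusted and adjusted was 0.71 and 0.70 at R² = 0, 0.70 and 0.74 at R² = 0.10, and 0.70 and 0.85 at R² = 0.30. With no effect, the rejection rate was about 0.04 to 0.05 either way. The units differ from Step 4 (total SD rather than residual SD), so the levels are not interchangeable, but the direction agrees.

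**Step 6, cost of adjusting.** With 81 patients in 3 arms there are 81 − 3 = 78 between-patient degrees of freedom. Stage takes 2, leaving 76. If motor performance is measured daily, Table 1 gives 1 + 1 + 8 + 1 + 1 + 1 = 13 occasions. Stage-by-visit then takes 2 × 12 = 24 of 78 × 12 = 936 within-patient degrees of freedom, the same 2 in 78. Steps 2 to 4 ignore this small cost. The simulation at R² = 0 puts it at about one point of power.

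**The case against.** **The analysis as written is valid.** This stands. Unstratified randomisation with an unadjusted comparison is unbiased and keeps its type I error, as Step 5 confirms.

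**Chance imbalance is not a second harm.** A reader might infer that uneven stages could imitate or hide a reward effect. Imbalance is indeed common: with 27 per arm, some two arms differ by at least 20 percentage points in their stage III share in about 25% of allocations if that share is one third. For d = 0.5, 1.0 and 1.5, the 95% range of the resulting shift is 1.96 × √(2 × (d²/6)/27) = 0.11, 0.22 and 0.33 residual SD, or 16%, 32% and 48% of 0.674. But this is the same variance as in Step 2. For d = 1.0, √(0.533² + 0.218²) = 0.576, the unadjusted half-width already tabulated. The net widening is 0.011, 0.043 or 0.092 residual SD, and the ordinary standard error already carries it.

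**The size is assumed.** This stands. Stage may not predict improvement at all, and setting the pegboard to each patient's own maximum could even narrow differences between stages. At d = 0.5 the gain is about two points of power, and the cost of adjusting takes back part of it. The calculation also uses a single change score, not the full visit schedule.

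**Covariates and strata may be in an unseen document.** This stands in part. The absence of a stratification factor from a condensed article is no fault in itself, and a fuller plan may add covariates. But the article does name a model for these outcomes, by group and without stage, and a fallback test that takes no covariate.

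**Stage-by-visit is expensive.** This has little force. Its 24 parameters come out of 936 within-patient degrees of freedom.

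**Conclusion.** The point holds as one of efficiency. A baseline severity measure that must be obtained for every patient is left out of the described pegboard and BBT analysis, and any stage-dependent improvement then inflates the error of the group-by-time test. The loss runs from nothing (d = 0) to the equivalent of 38% more patients (d = 1.5). It rests on equal thirds by stage and on assumed gains for which the documents give no figure.

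Two stronger readings are not supported. The trial's motor result is not biased and its false-positive rate is not raised. The primary outcome, the SRMS, is not touched: motor performance is listed among the secondary outcomes.

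The point is still worth acting on because precision is short. At 0.674 with 27 per arm, a pairwise two-sided t-test has about 68% power even with no stage effect, whereas the Sample size section plans "with an alpha value set at 0.05, power at 0.95". That gap is a separate matter, and this point does not depend on it.

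**What to change.** Before unblinding, prespecify Brunnstrom stage (III, IV, V) and stage-by-visit as fixed terms in the pegboard and BBT models, and confirm that the stage itself is entered on the case report form rather than only a tick for eligibility. If the data are non-normal, use a transformation or a rank-based model that keeps the covariate, in place of an unadjusted Kruskal-Wallis test. If a fuller analysis plan already does this, align the article's description with it.

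The change need not extend to STEF on this ground: the Statistical analysis section describes no STEF analysis and Table 1 does not schedule it.

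Separate envelope sets by stage are optional, and possible only if allocation is still open. The covariate adjustment does not depend on them.

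Cost: about two between-patient degrees of freedom and slightly more analysis work. No extra patients, visits or measurements are needed.
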